## Abstract

**Introduction::**

Peripheral facial palsy (PFP) results in weakness or paralysis of the affected side of the face. In Korea, there is a high demand for Korean medicine treatment for PFP. The clinical practice guidelines (CPGs) of Korean medicine for facial palsy were developed; however, there remains insufficient evidence to support the effectiveness and safety of Korean medicine treatment. Thus, this study aimed to evaluate the effectiveness and safety of Korean medicine treatment based on the CPGs in patients with acute PFP.

**Methods::**

This is a multicenter, prospective, observational study. The participants will be recruited from one Korean medicine hospital and eight Korean medicine clinics. The participants will receive Korean medicine treatments based on the CPGs, fill in survey questionnaires, and undergo electrophysiologic testing. The changes in House-Brackmann (H-B) grade, movement of the lip and eye, symptoms related to or accompanied by facial palsy, Facial Disability Index, EuroQol 5-dimension 5-level (EQ-5D-5L), and EuroQol Visual Analogue Scale (EQ-VAS), and the results of electromyography (EMG), electroneurography (ENoG), and Blink Reflex test will be analyzed. For the safety analysis, adverse events will be recorded, and for the feasibility analysis, the results of the Was It Worth It questionnaire will be assessed.

**Conclusion::**

We expect to draw real-world clinical data on the effectiveness and safety of Korean medicine treatment based on the CPGs in patients with acute PFP from this study. It would be the basis for complementing and improving the CPGs and provide the basis of clinical and policy decision-making.

**Trial registration::**

This study was approved by the Institutional Review Board of Kyung Hee University Korean Medicine Hospital (2021-06-005-001), and registered with the Korean Clinical Trial Registry (CRIS), Republic of Korea (KCT0006562).

## 1. Introduction

The facial nerve controls most of the muscles in the face and parts of the ear, and it also provides innervation to the lacrimal and salivary glands, as well as taste to the anterior two-thirds of the tongue.^[1]^ Peripheral facial palsy (PFP) generally refers to facial muscle weakness, which may lead to permanent damage to the facial nerve. Besides incomplete facial movement, patients may complain of other symptoms, such as postauricular pain, increase or decrease in tear, taste disorder, and hyperacusis. These symptoms and signs typically peak in the first week and then gradually resolve. Oral corticosteroids have traditionally been prescribed to reduce facial nerve inflammation, and because of the possible role of Herpes simplex virus 1 in the etiology, antiviral drugs can be given.^[2]^

According to the 2019 National Health Insurance Statistical Yearbook in Korea, a total of 111,089 patients visited Korean medicine hospitals and clinics due to facial nerve disorder, ranking 26th among all diseases.^[3]^ Although there is no recommendation regarding the effect of acupuncture in clinical practice guidelines (CPGs) of the American Academy of Otolaryngology-Head and Neck Surgery (AAO-HNSF) for Bell’s palsy^[4]^ and Cochrane review,^[5]^ many patients with PFP in Korea still visit Korean medicine hospitals and clinics for acupuncture and other Korean medicine treatments.

Because there is a high demand for Korean medicine treatment for PFP, the need for the CPGs of Korean medicine for PFP has emerged, which could be the standard for creating the basis of the effectiveness and safety of Korean medicine treatment in the real-world setting. Public clinical trials have been conducted to support the development of CPGs and produce real-world evidence in the healthcare field; however, public clinical trials conducted at the primary medical institution level are not enough. Additionally, in 2019, the CPGs of Korean medicine for facial palsy (FP)^[6]^ were developed, but there remains insufficient evidence to support the effectiveness and safety of Korean medicine treatment. Therefore, it is necessary to continuously supplement and improve the CPGs and strengthen the coverage of Korean medicine treatment within the current medical system.

In this study, patients with acute PFP will be recruited from 1 Korean medicine hospital and 8 Korean medicine clinics, and Korean medicine treatments will be provided based on the CPGs of Korean medicine for FP to identify the effectiveness and safety of Korean medicine treatment with real-world data.

## 2. Methods

### 2.1. Study design

This is a multicenter, prospective, observational study on Korean medicine treatment based on the CPGs in patients with acute PFP. PFP is diagnosed after excluding central facial palsy through symptoms and history taking. The participants will be recruited from 1 Korean medicine hospital and 8 Korean medicine clinics, from August 2021 to February 2022. To minimize selective bias, patients with facial palsy who visited the relevant medical institution are sequentially recruited and screened. The participants will receive Korean medicine treatments at each hospital or clinic, and fill in survey questionnaires from the baseline until six weeks later. The participants’ survey questionnaires include symptoms related to or accompanied by FP, Facial Disability Index (FDI), EuroQol 5-dimension 5-level (EQ-5D-5L), EuroQol Visual Analogue Scale (EQ-VAS), and Was It Worth It (WIWI) questionnaire. The participants will undergo electromyography (EMG), electroneurography (ENoG), and Blink Reflex test between visits 3 and 4, which is 2–3 weeks from the onset of PFP. The changes in House-Brackmann (H-B) grade and movement of the eyebrow and lip will be evaluated by investigators, and the treatments provided to the participants and adverse events will be recorded.

### 2.2. Inclusion criteria

The inclusion criteria are the following:

(1) Patients whose primary diagnosis is PFP (G51.0 Bell’s palsy; G51.8 Detailed facial neuropathy; G51.9 Facial nerve damage; and B022 Ramsay Hunt syndrome),(2) Patients with FP that occurred within 7 days,(3) Patients aged over 19 years.

### 2.3. Exclusion criteria

The exclusion criteria are the following:

(1) Patients participating in other clinical studies confirming the effectiveness of the intentional treatment,(2) Patients with a previous history of FP,(3) Patients with bilateral FP,(4) Patients who received Korean medicine treatment through other Korean medicine clinics or Korean medicine hospitals,

(If patients receive Korean medicine treatment though other Korean medicine clinics or hospitals, the investigators are not able to know what kind of Korean medicine treatments are performed to the patients, and it is difficult to determine the effectiveness of the treatments.)

(5) Patients who are expected to have difficulty adapting to clinical research schedules,

(Patients who are not able to visit once a week were excluded.)

(6) Patients who are expected to have difficulty understanding and responding to research questionnaires due to illiteracy and mental or physical weaknesses,

(Patients who are not able to understand this study and read and response the questionnaires were excluded.)

(7) Patients who are determined by the researchers to be unable to participate in the study.

### 2.4. Sample size

Based on similar studies, the clinical experiences of the investigators, and the preliminary research results,^[7,8]^ the sample size was determined. In this study, the therapeutic effect is defined as H-B grade 2 or lower. Assuming that the ratio of the patients with H-B grade 2 or lower after the treatments for 6 weeks is 80% (±10%, *P* = .05), considering the power of 80% and dropout rate of 15%, a total of 73 participants will be required. There were 2708 patients with PFP from 2006 to 2015 in Korea, and the average incidence rate over 10 years was 25.9 cases per 100,000 people.^[9]^ Therefore, the calculated 73 study subjects can be sufficiently recruited for the study period of about 6 months.

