### 2.13. Statistical analysis

For the primary outcome measure, including the H-B grading system, the proportion, and ratio of patients with H-B grade 2 or lower after the treatments will be analyzed.^[22,23]^

For the secondary outcome measures, including the movement of the eyebrow and lip, symptoms related to or accompanied by FP, FDI, EQ-5D-5L, EQ-VAS, WIWI questionnaire, and the results of EMG, ENoG, and Blink Reflex test, data will be analyzed using the mixed-effect model repeated measure, with visit time as a fixed factor and subject as a random factor.

Prognosis will be estimated using the results of EMG, ENoG and Blink Reflex test, and the correlation between the prognosis and the changes in H-B grade, movement of the eye and lip, symptoms related to or accompanied by FP, or the types of Korean medicine treatments provided will be analyzed using logistic regression analysis, considering age and sex as a potential confounders.

Since various Korean medicine treatments will be used, all treatments provided to the subjects will be recorded, and adverse events will be evaluated at every visit. For the safety analysis, the number of participants with and without SAEs will be estimated. The degree of symptoms and relevance to treatments will be analyzed, and SAE details will be described.

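### The 73 participants in section 2.4 come from a confidence-interval precision calculation; the 80% power stated beside the number plays no part in it and has no reference proportion, test or sidedness behind it

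*Protocol article*

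**What the plan says.** Section 2.4 (Sample size) defines therapeutic effect as H-B grade 2 or lower. Its planning assumption reads "Assuming that the ratio of the patients with H-B grade 2 or lower after the treatments for 6 weeks is 80" per cent, followed in brackets by ±10% and P = .05. The sentence ends: "considering the power of 80% and dropout rate of 15%, a total of 73 participants will be required". The section does not say whether ±10% is an interval half-width or a difference to detect. It names no reference proportion, no test and no sidedness.

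Section 2.1 (Study design) describes one cohort without a comparator: "This is a multicenter, prospective, observational study on Korean medicine treatment based on the CPGs in patients with acute PFP". For the primary outcome, section 2.13 (Statistical analysis) says only that "the proportion, and ratio of patients with H-B grade 2 or lower after the treatments will be analyzed".

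**The concern.** Power is the probability that a specified test rejects a specified null value when a specified alternative is true. For a single proportion it needs a reference value, a test and a significance level with its sidedness. Section 2.4 gives a power figure with only one of these, a 5% level of unstated sidedness. A single cohort whose primary analysis is described as a proportion is normally sized for precision, and the bracketed ±10% looks like a precision target.

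This sentence is the only justification given for the sample size. The article says the results should inform clinical and policy decisions. A reader who takes the power statement at face value could regard a result near 80% as the outcome of an adequately powered test of effectiveness. What the stated inputs provide is an estimate with a margin of about 10 points.

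**Working it through.** **Inputs, all from section 2.4:** expected proportion p = 0.80; ±10%, so d = 0.10; level 0.05; stated power 0.80; dropout 0.15; stated total 73.

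**Step 1: reproduce the 73 as precision.** For a 95% interval of half-width d, n = z² p(1 − p) / d².

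- n = 1.96² × 0.8 × 0.2 / 0.10² = 3.8415 × 0.16 / 0.01 = 61.46, rounded up to 62.
- Dropout: 62 / (1 − 0.15) = 72.94, rounded up to 73.
- Half-width at n = 62: 1.96 × √(0.16/62) = 0.0996, or 9.96 points.

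The match is exact and uses every stated input except power.

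**Step 2: try to reproduce 73 with 80% power.** The usual one-sample formula is n = [(z_α √(p0 q0) + 0.8416 √(p1 q1)) / 0.10]², where p0 is the null, p1 the true proportion and q = 1 − p. The four pairs below are assumptions, because the article fixes no null. Enrolled means evaluable divided by 0.85.

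| Null, true | Two-sided 5%: evaluable (enrolled) | One-sided 5%: evaluable (enrolled) |
|---|---|---|
| 70%, 80% | 153 (180) | 119 (140) |
| 80%, 70% | 137 (162) | 109 (129) |
| 80%, 90% | 108 (128) | 83 (98) |
| 90%, 80% | 86 (102) | 69 (82) |

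None gives 73. Variance at the null only, variance at the alternative only, the arcsine form, a continuity correction, dropout as n × 1.15, and a two-group comparison do not give it either. The nearest totals on the low side are 66 and 65, from a crude one-sided form that uses the variance at 90% alone. The nearest on the high side are 80 and 82.

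**Step 3: what 62 evaluable patients would give, as an illustration.** Power = Φ[(0.10 − z_α √(p0 q0/62)) / √(p1 q1/62)]. For null 70% and true 80%, two-sided: 1.96 × √(0.21/62) = 0.1141; (0.10 − 0.1141)/0.0508 = −0.277; Φ = 0.391.

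| Null, true | Two-sided: normal | Two-sided: exact | One-sided: normal | One-sided: exact |
|---|---|---|---|---|
| 70%, 80% | 39.1% | 39.9% | 53.4% | 52.5% |
| 80%, 70% | 50.3% | 39.5% | 61.1% | 50.4% |
| 80%, 90% | 50.5% | 57.3% | 66.7% | 57.3% |
| 90%, 80% | 69.1% | 60.1% | 76.9% | 72.0% |

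No entry reaches 80%. Only the crude one-sided form with the variance at 90% alone does (84%). That form leads to a total of 66 or 65, so it is not the source of 73.

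**Step 4: read power as assurance of precision.** The chance that the 95% interval from 62 patients has a half-width of 10 points or less, when the true proportion is 80%, is about 53% (Wald), 65% (Wilson) or 28% (Clopper–Pearson). This reading does not yield 80% either.

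**The case against.** The best defence is that nothing is wrong with the number. The arithmetic of 73 is right, precision is a sensible basis for a single observational cohort, and recruitment, endpoint and estimate stay the same whether or not the power clause is there. All of that stands. What remains is that the article states a property which its own inputs do not produce. This is a statement in the text and not an omission, so a fuller protocol or an analysis plan could add a test but could not make these inputs yield 73 through 80% power.

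A second objection is that power cannot be calculated without a null, so the percentages in step 3 belong to assumed scenarios. That is correct. Two of the four pairs also set the true proportion at 70% or 90%, not at the 80% that section 2.4 expects. The figures show that no ordinary reading of ±10% as a difference rescues the claim. They do not measure this study.

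A reader might be tempted to go further in two ways:

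- **That no hypothesis test is planned.** The article does not say so. Section 2.13 plans mixed models and logistic regression for other analyses, section 2.11 defines the primary outcome as changes in H-B grade, and a test may appear in a document that is not shown.
- **That nine sites make the interval wider by some stated amount.** The article gives no intraclass correlation and no site sizes, so the effect cannot be sized from it. Adjustment for site is a detail commonly left to the analysis plan. The most that can be said is that the ±10 points assumes independent patients.

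**Conclusion.** Section 2.4 is wrong as written, in one clause. The total of 73 is correct as a precision calculation: 62 evaluable patients give a 95% interval of about ±10 points around 80%, and 15% dropout brings the total to 73. The 80% power attached to it was not used in reaching the number and has no reference proportion, test or sidedness to support it.

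The exact match in step 1 rests on stated inputs only, apart from reading ±10% as the half-width of a two-sided 95% interval. The illustrative power of 39–69% (exact 40–60%) at two-sided 5%, or 53–77% (exact 50–72%) at one-sided 5%, rests on assumed nulls 10 points from the true value and on a sidedness that the article does not give.

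A reader might infer that the study is underpowered, with a true power of 39–69%, or that it must recruit more patients. The document supports neither: without a stated test the study has no defined power to fall short of, and 73 suits the estimation that section 2.13 describes.

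**What to change.** In section 2.4, delete the reference to 80% power. State instead that, with an expected proportion of 80%, 62 evaluable patients give a 95% confidence interval of about ±10 percentage points, assuming independent patients, and that 73 allows for 15% dropout. In section 2.13, add that the primary proportion will be reported with its 95% confidence interval.

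If a test of the primary proportion is in fact intended, state its reference proportion and sidedness, and give the power that 62 evaluable patients deliver for it.

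The cost is one sentence in each section. No more patients are needed. The only downside is that the stated figure becomes less favourable.

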### 2.5. Ethics

This study will be conducted in accordance with the Declaration of Helsinki and the Guidelines for Good Clinical Practice. Before obtaining consent, all patients will be provided with oral and written study information. This study was approved by the Institutional Review Board of Kyung Hee University Korean Medicine Hospital (KOMCIRB 2021-06-005-001) and registered with the Korean Clinical Trial Registry (CRIS), Republic of Korea (KCT0006562).

### 2.6. Consent and registration

The participants will be recruited from 1 Korean medicine hospital and 8 Korean medicine clinics. They will be provided with study information. After providing consent to the enrollment, eligibility criteria will be evaluated, and the participants will be assigned an identification number and registered as study participants. Registration will be closed when the planned number of participants has been reached.

### 2.7. Treatment

The participants will receive Korean medicine treatments based on the CPGs but will not receive any intentional treatments. The Korean medicine treatments may include acupuncture, electroacupuncture, pharmacopuncture, moxibustion, herbal medicine, and cupping. The investigators will keep a record of the treatments provided to the participants.

According to the CPGs,^[6]^ acupoints such as ST4, ST6, EX-HN5, TE17, GB14, SI18, LI4, and GB20 are frequently used for acupuncture treatment for FP, and other acupoints can also be used according to the patient’s symptoms and judgment of Korean medicine doctors. In addition, electrical stimulation can be applied to the acupoints. In case of herbal medicine treatment, Korean medicine doctors determine the prescription according to the condition and characteristics of each patient. Acupoints such as TE17 and GB12 can be used for wet cupping. Pharmacopuncture such as Bee venom and placenta, and moxibustion treatment can be applied on face and behind the ear.

### 2.8. Data collection

Data will be obtained by investigator assessment and participant survey at baseline and at specified follow-up times (Table 1).

**Table 1 T1:** Schedule of observations

		Observation Period						
Visit	Screening	1	2	3	4	5	6	7
**Week**	**0-1**	**0-1**	**1**	**2**	**3**	**4**	**5**	**6**
**Informed consent**	**●**							
**Demographics**	**●**							
**Vital sign and body measurement**	**●**							
**Medical history of facial palsy**	**●**							
**Medical history of underlying disease and medication**	**●**							
**Inclusion/Exclusion criteria**	**●**							
**House-Brackmann grading system**		**●**	**●**	**●**	**●**	**●**	**●**	**●**
**Movement of eyebrow and lip**		**●**	**●**	**●**	**●**	**●**	**●**	**●**
**Symptoms related to facial palsy**		**●**	**●**	**●**	**●**	**●**	**●**	**●**
**Symptoms accompanied by facial palsy**		**●**	**●**	**●**	**●**	**●**	**●**	**●**
**FDI**		**●**						**●**
**QoL (EQ-5D-5L, EQ-VAS**)		**●**						**●**
**WIWI questionnaire**								**●**
**EMG, ENoG, Blink reflex**				**●**				
**Adverse events**		**●**	**●**	**●**	**●**	**●**	**●**	**●**

### 2.9. Investigator assessment

The investigators, who are Korean medicine doctors working in the hospital and clinics participating in this study, will assess the changes in H-B grade and movement of the eyebrow and lip. All measurements and assessments will be performed at baseline and once a week until 6 weeks later.

### 2.10. Participant survey

The participants will fill in survey questionnaires at baseline and once a week until 6 weeks later. The questionnaires include symptoms related to or accompanied by FP, FDI, EQ-5D-5L, EQ-VAS, and WIWI questionnaire. The participants will fill in the questionnaires about symptoms related to or accompanied by FP at every visit, FDI, EQ-5D-5L, and EQ-VAS at the first and last visits, and WIWI questionnaire only will be at the last visit.

### 2.11. Primary outcome measurement

The primary outcome is the changes in H-B grade from baseline until 6 weeks later. The H-B grading system is the most widely used and accepted scale for motor function assessment that helps document the degree of paralysis from grade I (normal facial function) to grade VI (total paralysis)^[10]^ (Table 2). The reliability of H-B grading system for FP has been proven, and it has been used as a simple and robust method of assessing facial function.^[11]^

**Table 2 T2:** House-Brackmann grading system

Grade	Definition
I	Normal symmetrical function in all areas
II	Slight weakness noticeable only on close inspection
	Complete eye closure with minimal effort
	Slight asymmetry of smile with maximal effort
	Synkinesis barely noticeable, contracture, or spasm absent
III	Obvious weakness, but not disfiguring
	May not be able to lift eyebrow
	Complete eye closure and strong but asymmetrical mouth movement with maximal effort
	Obvious, but not disfiguring synkinesis, mass movement or spasm
IV	Obvious disfiguring weakness
	Inability to lift brow
	Incomplete eye closure and asymmetry of mouth with maximal effort
	Severe synkinesis, mass movement, spasm
V	Motion barely perceptible
	Incomplete eye closure, slight movement corner mouth
	Synkinesis, contracture, and spasm usually absent
VI	No movement, loss of tone, no synkinesis, contracture, or spasm

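### Baseline may fall anywhere in the week when signs are said to peak, so change from baseline depends partly on day of entry, and the stated models carry no term for time since onset

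*Protocol article*

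**What the plan says.** All references are to the protocol article.

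- **Natural course (1. Introduction).** "These symptoms and signs typically peak in the first week and then gradually resolve".
- **Entry (2.2).** "Patients with FP that occurred within 7 days".
- **First grade (Table 1 in 2.8).** Visit 1, which carries the first H-B grade, is placed at week 0-1, and visit 2 at week 1.
- **Schedule (2.9).** "All measurements and assessments will be performed at baseline and once a week until 6 weeks later".
- **Primary outcome as defined (2.11).** "The primary outcome is the changes in H-B grade from baseline until 6 weeks later".
- **Primary outcome as analysed (2.13).** The proportion and "ratio of patients with H-B grade 2 or lower after the treatments will be analyzed". The sample size in 2.4 rests on the same responder definition.
- **Secondary outcomes (2.13).** A repeated-measures mixed model "with visit time as a fixed factor and subject as a random factor".
- **Logistic regression (2.13).** Changes in H-B grade, other clinical measures and treatment types are related to electrophysiologic prognosis, "considering age and sex as a potential confounders".

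Neither the mixed model nor the logistic regression, as stated, includes time since onset.

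**The concern.** The entry window and the stated peak week are the same 7 days. A patient graded before the peak has a reference milder than the worst state reached; a patient graded at or after the peak does not. The same disease course with the same final grade can then give different changes, depending only on the day the patient presented.

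In a randomised comparison, entry day would tend to balance between arms. Here there is one uncontrolled cohort, and within-patient change is itself read as effectiveness. Patients come from nine institutions that may see them at different points in the first week, and treatments are chosen by each doctor for each patient (2.7). Entry day is therefore a plausible confounder where 2.13 relates treatment types and H-B change to prognosis, yet only age and sex are named.

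At stake is the meaning of H-B change and of change in eyebrow and lip movement, symptoms, FDI, EQ-5D-5L and EQ-VAS, all first measured at visit 1. The WIWI questionnaire and the electrophysiologic tests have no visit 1 value and are not involved.

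**Working it through.** **1. Does the sample size depend on baseline?** Inputs from 2.4: expected proportion 80%, margin ±10 points, alpha .05 (two-sided assumed), dropout 15%.

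- n = 1.96² × 0.8 × 0.2 / 0.1² = 61.46, rounded up to 62.
- 62 / (1 − 0.15) = 72.9, rounded up to 73.

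The stated 73 is reproduced. It rests on a proportion after treatment with no baseline grade in it, so the timing of baseline does not change it.

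**2. How many baselines could precede the worst grade?** The article gives neither the distribution of entry day nor the day of peak, so both are assumed. If entry is uniform over days 0 to 7, the share entered before the peak is (peak day) / 7. If entry is uniform over days 3 to 7 only, it is (peak day − 3) / 4, and 0 for a peak on day 3 or earlier.

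| Assumed peak day | Entry uniform, days 0-7 | Entry uniform, days 3-7 |
|---|---|---|
| 1 | 1/7 = 14% | 0% |
| 3 | 3/7 = 43% | 0% |
| 5 | 5/7 = 71% | 2/4 = 50% |
| 7 | 7/7 = 100% | 4/4 = 100% |

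If peak day is itself uniform over days 0 to 7, independently of uniform entry, the share is about 50%.

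**3. What does entry day do to one patient's change?** Assumed course: grade II on day 0, worsening by one grade a day to grade V on day 3, unchanged to day 7, and grade II at the last visit.

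| Entry day | Grade at visit 1 | Change to grade II |
|---|---|---|
| 0 | II | 0 |
| 1 | III | −1 |
| 2 | IV | −2 |
| 3 to 7 | V | −3 |

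Course and final grade are identical in every row. The responder outcome is the same in every row too: the patient ends at grade II and counts as a success.

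**4. Which clock do the visits follow?** Section 2.1 places the electrophysiologic tests "between visits 3 and 4, which is 2–3 weeks from the onset of PFP", which suggests weeks counted from onset. Sections 2.9 and 2.11 count from baseline.

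- Onset clock: visit 2 is at about day 7 for everyone, and baseline to week 6 spans about 5 to 6 weeks, depending on entry day.
- Baseline clock: visit 2 is on days 7 to 14 from onset, and the last visit is 6 to 7 weeks from onset.

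Either way, the day of entry also shifts an interval that the change measures take as common to all patients.

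**The case against.** The strongest objection is that the planned primary analysis is untouched. Section 2.13 analyses the proportion at H-B grade 2 or lower, 2.4 sizes the study on it, and it has no baseline term. This stands. A reader might infer that the primary result or N = 73 is biased; steps 1 and 3 show that neither is, by this route. Nor does 2.13 state a repeated-measures model for H-B: that model is given for the secondary outcomes only.

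Second, the magnitude is assumed. This stands as well. A reader might multiply shares of 43% to 100% by one grade still to be lost and conclude that mean H-B change is understated by about 0.4 to 1.0 grade. That combines an entry distribution, a peak day and an average loss, none of which the article gives. Nor does the text show that early entrants will look worse at visit 2, since an early peak may have partly resolved by then.

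Third, a baseline taken before the peak understates recovery from the worst point, which is conservative in a single-arm study. That is fair for average change. It gives no protection in the logistic regression, where an unlisted confounder can act in either direction.

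Fourth, a condensed article leaves covariate detail to a fuller plan. The concern is not silence, however: 2.11 fixes the reference, and 2.13 names the model factors and the confounders.

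**Conclusion.** The point holds in limited form. The overlap between entry window and peak week is in the protocol's own text, and change from visit 1 therefore depends partly on day of entry. Some baselines, possibly many, precede the worst grade. The share (0% to 100% under the assumptions tried) and the resulting error in grades cannot be determined from the document.

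The affected quantities are H-B change as worded in 2.11, H-B change in the logistic regression, and change from visit 1 in movement, symptoms, FDI, EQ-5D-5L and EQ-VAS. The responder proportion and the sample size are not affected by this route. The change is worth making because the information needed is already required for eligibility, but this is not a flaw in the main planned analysis.

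**What to change.** In 2.13:

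1. Add days from onset to visit 1, and its interaction with visit, to the repeated-measures models for eyebrow and lip movement, symptoms, FDI, EQ-5D-5L and EQ-VAS. Adjusted change can then be reported at a stated entry day.
2. Add days from onset to visit 1 to age and sex as a confounder in the logistic regression.
3. Present any H-B change from baseline by, or adjusted for, days from onset to visit 1.

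These terms show and adjust for dependence on entry day. They do not recover a worst grade that was never observed.

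Change from the worse of the visit 1 and visit 2 grades should be at most a labelled sensitivity description. Visit 2 follows the start of treatment, it can still miss the peak (entry on day 1 with the worst grade on day 5 puts visit 2 on day 8 under the baseline clock), and taking the worse of two noisy gradings inflates apparent improvement.

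**Cost.** No new visit or test is needed: timing of onset must be established for inclusion criterion 2. With days from onset entered linearly and visit as categories, an outcome measured at all seven visits takes 1 + 6 = 7 extra parameters, and one measured at the first and last visits takes 1 + 1 = 2. The logistic regression takes one. With about 62 evaluable patients (73 × 0.85 = 62.05) this is affordable, at some loss of precision.
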